**Appendix-iv: CBVP-Education manual to trainers**

**Introduction**

Couples education package is a set of preventive messages designed to help foster a process of change to reduce intimate partner violence during pregnancy amongst couples in Hadiya Zone, Southwest, and Ethiopia. The contents included in the education manual to prevent intimate partner violence in pregnancy includes the following

- Gender-based violence
- Violence against women
- Intimate partner violence
- Types of intimate partner violence (physical, sexual, and psychological or emotional violence)
- Magnitude of intimate partner violence in pregnancy
- Inequitable gender norms and consequences
- The relationship between intimate partner violence and power and control
- Common triggers of IPV in pregnancy
- Uhhealthy and healthy relationship
- Common triggers of IPV and ways to challenge the triggers
- Effective communication and conflict resolution in relationship

**Structure of the sessions**

There are 6 total sessions in the anual. Each session is a maximum of 60 minutes

**Couples take- home exercises and reflections**

All sessions contain take-home exercises that are assigned at the end of the session, and to help the couples reflect upon and apply new ideas in their own lives. Research shows that doing exercises at home following training significantly increases the effectiveness of the program. Each session, likewise, starts with a reflection of the take-Home exercise. The format of this reflection is the same for each session, with different guiding questions to facilitate debriefs.

**Participants**

The manual will be implemented with couples in selected clusters of intervention. The education takes place at health center or health post in group.

**Supplies needed**

Simple training supplies including, parker, flip chart paper and poster are needed for the training. Sessions are designed with the understanding that they will be implemented in an enclosed workshop space. However, accommodations can be made if that is not available. It is recommended to arrange chairs in a semi-circle to help build connections and discussion between couples and HEW educator.

**Language**

The Amharic or Hadiyisa (local language) will be used in this training manual according to the participants’ preference.

**The training manual objective**

1. To enable the participants describe the GBV, VAW, IPV, IPV, types of IPV and Magnitude of IPV
2. To enable the couples to describe the extent of intimate partner violence
3. To enable the couples to explain adverse consequences of intimate partner violence during pregnancy
4. To enable couples to describe common triggers of violence and state the common ways to challenge the triggers of IPV
5. To enable the couples to describe inequitable gender norms related to IPV during pregnancy
6. To enable the couples to describe an effective communication skills and nonviolent ways of conflict resolution

The CBVPE session schedules, titles and objectives

| Session schedule by Gestational ages | Session title | Session objectives |
| --- | --- | --- |
| 1^st^ session  (13-16 weeks) | Program introduction & understanding GBV, VAW and IPV | To describe the goal of the program  To define GBV, VAW and IPV  To explain types and magnitude of IPV |
| 2^nd^ session  (17-20 weeks) | Consequences and common triggers of IPV during pregnancy | To describe adverse maternal and new-born consequences of IPV during pregnancy  To explain economic and social consequences of IPV during pregnancy  To identify common triggers of IPV  To state the ways to challenge triggers of IPV |
| 3^rd^ session  (21-24 weeks) | Inequitable gender norms related to IPV during pregnancy | To describe common gender norms for women and men  To differentiate gender and sex  To understand how inequality gender norms contribute to IPV during pregnancy  To describe the ways to challenge and transform inequitable gender norms |
| 4^th^ session  (25-28 weeks) | Unhealthy and healthy relationship | To differentiate healthy and unhealthy behaviors in marital relationship  To state important characteristics of healthy relationships |
| 5^th^ session  (29-32 weeks) | Power and control in relationship &  Joint decision making | To define power and control  To describe healthy power balance within relationship  To explain benefits of joint decision making  To describe and apply seven strategies to joint decision making |
| 6^th^ session  (33-36 weeks) | Communication & conflict resolution | To describe effective communication skills in relationship  To explain nonviolent ways of conflict resolution in relationship |

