**6.15 Description of the Intervention**

The purpose of the study is to provide community-based health education to couples on violence prevention to reduce intimate partner violence during pregnancy. A group health education on violence prevention, including intimate partner violence, for couples in the intervention group will be provided in a place center for the participants. 16 kebels found in the four districts will be the study clusters.

A package of health education messages on violence prevention will be provided to couples living in the intervention arm. The package was adapted from a psychosocial education study conducted among couples (Mutisya et al., 2018) and gender transpormative education on intimate partner violence in Tanzania (Harvey et al., 2021). The health education messages will be conducted by health extension workers who are working in intervention clusters (kebeles). Eight health extension workers will be selected for the intervention (CBVP education). The following criteria will be used to recruit health extension workers:

- Health Extension Workers who are female
- able to speak Amharic and the local language (Hadiyisa).
- willing to participate in the study period
- Good interpersonal and communication skills
- Having participated in a survey previously

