**6.15.1 Couple education contents and sessions**

**Control group (study group 1):** no intervention will be provided for these clusters (kebeles) from the research group. However, the control group will not be restricted from the standard health extension package services provided by health extension workers.

**Couples GBV prevention education group (study group 2):** in this group, the couples (pregnant women and their male partners) will be educated on:

- Gender-based violence
- Violence against women
- Intimate partner violence
- Types of intimate partner violence (physical, sexual, and psychological or emotional violence)
- Magnitude of intimate partner violence in pregnancy
- Inequitable gender norms and consequences
- The relationship between intimate partner violence and power and control
- Common triggers of IPV in pregnancy
- Uhhealthy and healthy relationship
- Common triggers of IPV and ways to challenge the triggers
- Effective communication and conflict resolution in relationship

The couple’s education will be provided every fourth week by the health extension workers, assisted by the researcher. Baseline data will be collected from 10 to 12 weeks of gestation. The education services will be provided in groups, and each participant has six contacts with the educator. The contents and sessions for couple education are illustrated below in Figure 7.

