**6.15.3 Intervention fidelity**

Intervention fidelity refers to the degree to which components of intervention are executed as designed. To enhance the intervention's fidelity, we will implement the following actions: a trainer manual has already developed; extensive training will be provided for interventionists (HEWs); spot checks will be conducted by field supervisors during each intervention session; and feedback meetings with interventionists will be held after each session. A fidelity checklist that addresses adherence and intensity of the intervention will be used to evaluate intervention fidelity at the end of each session.

Table 2:summary of the intervention package and implementation process

| **Session** | **Content of the message** | **Dose** | **Strategy of delivery** | **Frequency** | **Compliance parameters** | **Responsible person** |
| --- | --- | --- | --- | --- | --- | --- |
| Session 1  (13-16 weeks) | - Introducing each other - Gender based violence (what is it) - Violence against women(what is it) - Intimate partner violence(what is it ) - Types of intimate partner violence - Physical, sexual and psychological - Magnitude of IPV - Summarization - Introduction on take home-exercise next - Appointment to next session | 60 minutes | • Brain storming • Lecture • Question and Answer  **.**Take-home exercise and reflections | Once | -% couples participated | Researcher, Supervisors & Health extension workers |
| Session 2  (17-20 weeks) | - Refelection on take home exercise and recap - Maternal and new born consequences of IPV - Economic and social consequences - Family and dependents consequences - Common triggers of IPV during pregnancy - Ways to challenge triggers of IPV - Introduction on take-home exercise - appointment to next session | 60 minutes | • Brain storming • Lecture • Question and Answer  **.**Take-home exercise and reflections | Once | -% -% couples participated | Researcher, Supervisors & Health extension workers |
| Session 3  21-24 weeks | - Reflection on take home exercise - Common gender norms for women and men - Gender and sex - Inequality gender norms related to IPV during pregnancy - The ways to challenge inequitable gender norms - Introduction on take-home exercise and appointment to next session | 60 minutes | • Brain storming • Lecture • Question and Answer  **.**Take-home exercise and reflections | Once | -% -% couples participated | Researcher, Supervisors & Health extension workers |

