| Session 4  (25-28 weeks) | - Recap and reflection on take home exercise - Healthy and unhealthy behaviors in marital relationship - Important characteristics of healthy relationships - Introduction on take-home exercise and appointment to next session | 55 minutes | • Brain storming • Lecture • Question and Answer  **.**Take-home exercise and reflections | Once | -% -% couples participated | Researcher, Supervisors & Health extension workers |
| Session 5  (29-32 weeks) | - Recap and Reflection on take-home exercise - Define power and control - Healthy power balance within relationship - Benefits of joint decision making - Seven strategies to joint decision making - Take | 60 minutes | • Brain storming • Lecture • Question and Answer  **.**Take-home exercise and reflections | Once | -% couples participated | Researcher, Supervisors & Health extension workers |
| Session 6  33-36 | - Recap and reflection on take home exercise - Effective communication skills in relationship - Nonviolent ways of conflict resolution in relationship   Summarization and close up | 60 minutes | • Brain storming • Lecture • Question and Answer | Once | -% couples participated | Researcher, Supervisors & Health extension workers |
|  | Provision of printed take-home materials | -Poster | - | Delivered during in each training session | -% of couples received posters | Researcher, Supervisors & Health extension workers |
|  | **End line data collection** | - | - | at 8^th^ month of intervention | % pregnant mother and their husbands interviewed | Researcher, supervisors and data collectors |

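### The step guides, handout and Amharic manual script a different education package from Table 2 and the manual's own schedule, mainly in sessions 3 to 6

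*Protocol*

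**What the plan says.** Three places in the protocol agree on the content of sessions 3 to 6: Table 2 (section 6.15.3, Intervention fidelity), the session schedule in Appendix IV and the time table that follows it. Table 2 gives session 3 "Inequality gender norms related to IPV during pregnancy" together with common norms, gender and sex, and ways to challenge norms. Session 4 is healthy and unhealthy relationships. Session 5 is power and control with "Seven strategies to joint decision making". Session 6 is communication and nonviolent conflict resolution. The schedule's objectives repeat this, and the manual's general objectives include describing "inequitable gender norms related to IPV during pregnancy".

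The topic list in section 6.15.1 includes "Inequitable gender norms and consequences" and conflict resolution. The lists in section 6.19 (Training) and the Appendix IV introduction repeat both. Joint decision-making is on none of the three. Section 6.15 says the package was adapted in part from "gender transpormative education on intimate partner violence in Tanzania".

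On delivery, section 6.15.3 says "a trainer manual has already developed" and "A fidelity checklist that addresses adherence and intensity of the intervention will be used". The Language paragraph of Appendix IV says "The Amharic or Hadiyisa (local language) will be used in this training manual", according to participants' preference.

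The later pages of Appendix IV, which take the educator through each session step by step, give sessions 3 to 6 other topics. So do the English handout (Annex V), the Amharic manual (Annex viii) and the Amharic handout (Annex ix).

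**The concern.** In an education trial the script is the intervention. Here the summary and the script of the same manual disagree, and the Amharic version, in one of the two languages of delivery, carries only the scripted content. The step guides also tell educators to repeat a session until couples answer at least 75 percent of the questions, which reinforces whatever content the guide contains.

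If educators follow the guides, the trial estimates the effect of a package without a gender-norms session and without the joint-decision material, although the protocol describes both. The joint-decision part bears on a declared secondary outcome: section 6.17 scores women's autonomy by whether the woman decides alone or jointly. Anyone who later wanted to repeat the package, or add it to the health extension package as section 4 foresees, could not tell from this document which version was tested.

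**Working it through.** No sample size or power figure is involved. The check is a comparison of texts and a count. The text of Figure 6 came through in broken order and is not used as evidence.

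**Topics**

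| Session | Table 2, schedule and time table | Step guides, handout and Amharic texts |
|---|---|---|
| 3 | Gender norms | Pregnancy consequences, effects on perpetrators and society, male involvement |
| 4 | Healthy and unhealthy relationships | Power and control, healthy power balance or relationship, husband's role |
| 5 | Power and control, joint decisions | Triggers (the English guide adds healthy relationship and husband's role) |
| 6 | Communication, conflict resolution | Women's empowerment |

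The main topic matches in none of the four sessions. Part of this is reordering: power is planned for session 5 and scripted in session 4, healthy relationships appear in guides 4 and 5, and consequences and triggers belong to session 2. Women's empowerment is in no English plan, but it is in the Amharic manual's own objectives and session table.

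**Objectives of the schedule with an entry in the English step guides, counted generously**

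| Session | Objectives | With an entry | Without |
|---|---|---|---|
| 3 | 4 | 0 | 4 |
| 4 | 2 | 2 (healthy relationship, guides 4 and 5) | 0 |
| 5 | 4 | 2 (power and control, power balance, guide 4) | 2 (both on joint decisions) |
| 6 | 2 | 0 | 2 |
| Total | 12 | 0 + 2 + 2 + 0 = 4 | 4 + 0 + 2 + 2 = 8 |

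**What survives in the handout for those 8**

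- Joint decisions: a take-home question on who decides, a line on couples deciding together, and a tip to decide money matters jointly. The tip is one of five on balancing power. The seven strategies are not listed anywhere in the document.
- Communication and conflict: a tip on good communication, an exercise on disagreements, and advice under triggers to talk things over. The Amharic handout has equivalents of all three.
- Gender norms: no session and no dedicated page. Only loosely related lines exist, on husbands sharing household chores (session 4) and on ending discrimination and sharing household responsibility (session 6).

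**Sessions 1 and 2.** The English guides for these sessions match the schedule in topic and minutes. The other texts do not. The handout's session 2 has no triggers, which appear only on a later page, and most newborn consequences are on its session 3 page. The Amharic session 2 also omits triggers, and the Amharic session 1 adds maternal health.

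**Stated minutes**

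| Session | Table 2 | English time table | English guide | Amharic session table |
|---|---|---|---|---|
| 1 | 60 | 60 | 60 | 45 |
| 2 | 60 | 60 | 60 | 40 |
| 3 | 60 | 60 | 45 | 45 |
| 4 | 55 | 55 | 45 | 45 |
| 5 | 60 | 55 | 40 | 40 |
| 6 | 60 | 60 | 40 | 40 |

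The Amharic manual also gives 60 to 90 minutes per session in its general description.

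**The case against.** The strongest reply is that this is annex text that was not updated, and that the trial has ways to catch it. Educators receive three days of training on a list that includes gender norms and conflict resolution. The researcher assists the sessions (section 6.15.1) and is named with the supervisors as responsible for each one (Table 2). Spot checks and feedback meetings are planned for every session. Section 6.14 says the message will be based on baseline findings, so content may still be adjusted. All of this stands, and it makes uncorrected delivery from the script less likely. It does not supply the missing scripts or the seven strategies, and joint decision-making is not on the training list.

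Several stronger readings are tempting, and the documents do not support them:

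- **The manual is final.** The statement that it is already developed does not rule out revision, given section 6.14. No Hadiyisa manual is shown either.
- **The fidelity checklist has two rival references.** The checklist is not shown, and the same section contains Table 2, which is its natural reference. The protocol simply does not say so.
- **Users of the Amharic texts meet nothing from session 6.** The Amharic handout holds fragments on communication and disagreement. They are thin and misplaced, but present.
- **Couples would receive a shorter dose.** The minutes are suggested times that conflict on paper and say nothing about time delivered.
- **The handout drops session 5.** Its second session 4 heading is a mislabel; the Amharic handout numbers the same page 5.

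**Conclusion.** The contradiction is real and lies in current text. The step guides have no entry for 8 of the 12 objectives set for sessions 3 to 6. Gender norms have no session or dedicated page, and the seven joint-decision strategies are named but never listed. Joint decisions, communication and conflict resolution survive only as handout fragments. The mismatch is not confined to sessions 3 to 6, because session 2 of the handout and sessions 1 and 2 of the Amharic manual also depart from the plan.

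The count rests on generous crediting of the step guides. What counts as a handout fragment is a matter of judgement, so no firm number is put on that. Which version educators would follow is unknown, so the conclusion is that the delivered package could differ from the described one, not that it would.

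A reader might infer that the trial's comparison is compromised. It is not: randomisation and the intention-to-treat analysis are unaffected. What is uncertain is which package the estimated effect belongs to. That is worth settling before educators are trained.

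**What to change.** Before educator training, choose one package and make every text describe it.

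If Table 2 is intended, align the step guides, handout and Amharic manual and handout with Table 2 and the schedule for **all six sessions**:

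- Move triggers and newborn consequences into session 2 of the handout and Amharic texts. Rewriting only sessions 3 to 6 would remove triggers from them altogether.
- Add scripts for gender norms, for joint decisions with the seven strategies written out, and for communication and conflict resolution.
- Add joint decision-making to the topic lists in sections 6.15.1 and 6.19 and the Appendix IV introduction.
- Set one duration per session in every text.

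If the scripted package is intended, change Table 2, the schedule, the time table and the three topic lists instead.

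In either case, state in section 6.15.3 that Table 2 is the reference for the fidelity checklist.

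The cost is editing and re-translation. Design, sample size, outcomes and analysis stay as they are.

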**Contents of the session and time allocated**

| **Activity** | **Allocated time** |
| --- | --- |
| **Session 1( 13-16 weeks of gestational age)** | **60 minutes.** |
| - Introducing each other | 10 minutes |
| - Gender based violence (what is it) - Violence against women(what is it) - Intimate partner violence(what is it ) - Types of intimate partner violence - Physical, sexual and psychological - Magnitude of IPV - Take home execises | 40 minutes |
| Summarization and appointment to next session | 10 minutes |
| **Session 2 (17-20 weeks of gestational age)** | **60 minutes** |
| - Recap and reflection on take home exercise | 10 minutes |
| - Adverse maternal and new-born consequences of IPV during pregnancy - Economic and social consequences of IPV during pregnancy - common triggers of IPV - The ways to challenge triggers of IPV | 40 minutes |
| - Introduction on take-home exercise and appointment to next session | 10 minutes |
| **Session 3 (21-24 weeks of gestational age)** | 60 minutes |
| - Recap and reflection on take home exercise | 10 minutes |
| - Common gender norms for women and men - Gender and sex - Contribution of inequality gender norms to IPV during pregnancy - Ways to challenge and transform inequitable gender norms | 40 minutes |
| - Introduction on take-home exercise and appointment to next session | 10 minutes |
| **Session 4 (25-28 weeks of gestational age)** | 55 |
| - Recap and reflection on take home exercises | 10 minutes |
| - Healthy and unhealthy behaviors in marital relationship - Important characteristics of healthy relationships | 35 minutes |
| - Introduction on take-home exercise and appointment to next session | 10 minutes |
| **Session 5 (29-32 weeks of gestational age)** | 55 minutes |
| - Recap and reflection on take home exercises | 10 minutes |
| - Power and control in relationship - Healthy power balance in relationship of couples - Benefits of joint decision making - Strategies to joint decision making | 35 minutes |
| - Introduction on take-home exercise and appointment to next session | 10 minutes |
| **Session 6(33-36 weeks of gestational age)** | **60** |
| - Effective communication skills in relationship | 10 minutes |
| - Nonviolent ways of conflict resolution in relationship | 35 |
| - Acknowledgement and close up | 15 minutes |

**Session 1: Introduction to Gender Based Violence (GBV), Violence against Women (VAW) and Intimate partner violence (IPV)**

**Session one will be conducted first day or contact**

**Suggested time: 60 minutes**

**Session objective**

- To enable the couples to define a GBV, VAM and IPV
- To describe the types of IPV in pregnancy
- To explain the magnitude of IPV during pregnancy

**Activity**

**Steps**

1. Getting to know the HEW educator and couples on

2. Warmly welcome the couples to the first education session.

3. Introduce the process: today we will begin introduction to GBV, VAW and IPV. I will be here to guide the process. However, your participation will propel us forward. Each of us brings something unique to this space—our character, our ideas, and our experiences. Your contributions are what will enrich this process and give it meaning in your lives.

4. Prepare the materials like note book, pen and poster.

5. Start the teaching on the given topic

- What is GBV?
- What is VAW?
- What is IPV?
- Types of IPV
- Magnitude of IPV

6. Give time for questions or ask questions whether the couples understand or not

Make sure that the couples responded at least 75 percent of the questions asked

If the couples do not respond at least 75 percent of questions raised by the trainer, repeat the session for another time.

7. Give take home exercise, appoint for the next session and acknowledge the couples for their participation.

